#### Light therapy effectively treats acute sad and correction of circadian phase is mechanistic of its antidepressant effects

Light therapy (LT) is the established, most researched, acute SAD treatment. Meta-analyses show that 53% of SAD patients fully remit (and 47% do not) over an LT trial [15]. Clinical practice guidelines recommend solo LT as a first-line acute SAD treatment and reinitiating daily LT each fall from first symptom until spontaneous springtime remission [16, 17]. However, only 41% of those treated acutely with LT continue using it over subsequent winters [18]. Several studies support circadian rhythm disturbances in SAD patients, with their circadian phase occurring either later (phase delayed) or, less commonly, earlier (phase advanced) compared to their euthymic circadian phase position following remission with LT [19–22] or to healthy individuals in winter [19, 22]. As restoring the correct phase of circadian rhythms is supported as LT’s mechanism of action [15, 23–25], circadian phase measures are established biomarkers of LT’s target and effect. We will use the best established method, dim light melatonin onset (DLMO), along with wrist actigraphy, an objective measure of sleep/wake patterns, to calculate Phase Angle Difference (PAD) = DLMO–mid-sleep [21].

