#### Light therapy (LT)

Participants attend an initial instructional session that follows a script to explain the treatment rationale and assembly/position of the light box. These will be conducted by the (unblinded) P.I. in small groups of 2–4 subjects for efficiency. Effective fall/winter of 2020–2021, the P.I. posted a video recording of the instructional session on the lab’s private YouTube channel for those randomized to light therapy to watch remotely, due to the COVID-19 pandemic. In their homes, LT participants will use the SunRay (SunBox Company, Gaithersburg, MD), a standard device (23” × 15½”× 3¼”) with an ultraviolet shield that emits 10,000-lux of cool-white fluorescent light to the retina when the user is within 18 inches. Each of the 6 weeks, participants will complete the Light Therapy Side Effects Questionnaire used in our prior studies to assess the presence and severity of any side effects attributed to LT and self-reported times for onset of sleepiness, onset/offset of actual sleep, and desired times for onset/offset of sleep over the previous week. Side effects associated with LT are generally mild and can include headache (19%), eyestrain (17%), and feeling “wired” (14%) [46]. Although individuals typically respond within 4 weeks of initiating LT or not at all [16], our LT protocol will be maintained for 6 weeks to match CBT-SAD’s duration. To circumvent ethical concerns of discontinuing LT during the winter (when relapse is likely) [1], participants are encouraged to keep using the light box and bring it to the lab for servicing in May (to check the bulbs against a photometer and download adherence data). In an effort to reduce access to a suitable device as a potential confound, we will offer access to our light boxes to LT participants in winters 2 and 3 and to CBT-SAD participants crossed into LT in winter 2 for use in winter 3.

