### Provisions for post-trial care {30}

One human subjects issue in this work is balancing the need for treatment integrity over the follow-up interval with the need for re-treatment. A rigorous test of our aims requires steps to increase the likelihood that treatment over the follow-up interval is consistent with study treatment (i.e., that LT subjects are encouraged to continue light therapy each fall/winter and that CBT-SAD subjects are encouraged to keep using the skills learned in CBT-SAD on their own without a therapist). However, we recognize that we cannot ethically proscribe treatment in the interim and that we are accountable for directing them to resources if there is a need for re-treatment. We have developed an approach that attempts to balance these issues. (By design, one way we will deal with this is the cross-over at winter 2 for subjects who evidence a SAD recurrence at the winter 2 follow-up).

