As a step to increase the likelihood that treatment in the interim is consistent with initial study treatment, we will use standardized procedures for instructing participants at the end of study treatment. The first week of September, we will mail standardized letters, signed by the PI, to all participants treated the winter before prompting them to resume study treatment and to pursue new treatments only if needed. Both the CBT-SAD and LT letters include the same, standardized safety net in providing contact information for local mental health centers and treatment providers should they require more formal treatment. The letter to CBT-SAD-treated participants encourages them to keep using the skills learned in the CBT-SAD treatment on their own (without a therapist). The letter to LT-treated participants encourages them to re-initiate daily LT upon onset of the first depressive symptom in the coming fall/winter by either [1] borrowing one of our light boxes or [2] purchasing a device. Should they wish to purchase their own light box, we provide contact information for LT manufacturers with a list of specifications to match our devices (i.e., full-sized units emitting 10,000-lux cool-white light through UV filter). For either scenario, we ask the participant to identify a professional to whom they could turn in the event of side effects (since we will no longer monitor side effects and make prescription adjustments, as we did during acute treatment). LT participants may choose whether or not to have the PI provide a signed, generic letter that the participant may submit to his or her health insurance company to seek reimbursement for the cost of a light box. Participants crossed from CBT-SAD to LT at winter 2 will receive the standard LT letter the next September (winter 3), and participants crossed from LT to CBT-SAD will receive the standard CBT-SAD letter the next September.

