##### Winter 2 and 3 follow-up procedures

Follow-up assessments will occur in January of the next two winters (in winters 2 and 3). Testing in January reflects when the vast majority of SAD patients are in episode and when there are sufficient weeks left in the winter to treat them with the alternate modality if we detect a recurrence (i.e., 100% of SAD patients had an annual pattern of depression onset between September and January, 0% remitted before January, and only 22% remitted in January or February) [1]. Consistent with intent-to-treat principles, we will attempt to collect data on all enrolled subjects, including dropouts and those withdrawn from protocol. Participants will be interviewed by a clinical graduate student blind rater with the SIGH-SAD and the SCID-5-RV mood disorders module to assess for a major depressive episode in the interval from treatment endpoint to winter 2 and from winter 2 to winter 3. Participants will be assessed on biomarkers, questionnaire outcomes (BDI-II, BAI, Q-LES-Q, SDS, and MOS-SF-20), and the questionnaires we used in our prior studies to assess treatment utilization in the interim.

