## Statistical methods

### Statistical methods for primary and secondary outcomes {20a}

#### Data analysis

##### Aim 1

Logistic regression will be used to assess the effectiveness of treatment with either CBT-SAD or LT on depressive episode recurrence at winter 2. Covariates will be included in some analyses to assess the effect of treatment on outcomes after adjustment for any ongoing treatment reported at follow-up, such as any new treatment, psychotherapy, light therapy use in the CBT-SAD group, and antidepressant medication as in [name] et al. [14]. An intent-to-treat analysis will be conducted, using multiple imputation (MI) of missing next winter SIGH-SAD scores. Imputed scores will be used to classify depression recurrence status for individuals who dropped out or were lost to follow-up. Imputed values will be generated using the fully conditional specification (FCS) method to obtain regression estimates based on baseline and post-treatment SIGH-SAD (and component 21-item HAM-D and atypical subscale scores), demographic variables, comorbidity, and other baseline patient characteristics. Imputation will be done separately for the CBT-SAD and LT groups because data from our prior study indicate that the relationships between some of these variables and next winter recurrence differ in the two treatments. Ten data sets with imputed values will be generated and a dichotomous recurrence variable will be computed for each subject based on SIGH-SAD criteria. Logistic regression models will be fitted to each of the ten data sets and their parameter estimates will be combined using MI inference methods [43]. SAS PROC MI and PROC MIANALYZE will be used to carry out the imputation and analysis. The “missing at random” assumption of the MI analysis is valid if the imputation model is predictive of outcome. However, if we have an appreciable amount of missing data at follow-up, we will perform a sensitivity analysis using the pattern-mixture model approach (NMAR option in SAS 13.1) to assess the validity of the MI results.

Similar analyses will be performed to compare winter 3 outcomes in the CBT-SAD and LT subjects who did not have a winter 2 recurrence. Secondary analyses will examine the effects of treatment adherence within each treatment and the effect of therapist and therapy group within the CBT-SAD condition.

##### Aim 2

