To examine mechanistic differences between CBT-SAD and LT, mixed effects linear regression with subject as a random effect will be used to model biomarker changes during treatment as a function of time, treatment, and their interaction. We will also model the relationship between biomarker change and change depressive symptoms as a function of treatment by letting the regression coefficient differ between CBT-SAD and LT. This will provide a test of whether potential mediators of effect are treatment-specific. The predictive value of biomarkers at baseline, their pre-post treatment change, and the persistence of the change at follow-up will be examined using logistic regression (for post-treatment remission and winter 2 recurrence) and linear regression (for SIGH-SAD and BDI-II scores) with post-treatment and winter 2 outcomes as dependent variables. Interactions between the biomarkers and treatment will be used to test if the associations with outcomes differ in the CBT-SAD and LT groups. Adherence will be included in ancillary analyses to test its effect on the relationships of treatment with biomarkers and LT or CBT-SAD outcomes. The relationships between biomarkers and outcomes will be validated by examining how well they predict post-treatment and winter 3 outcomes for subjects who experience a recurrence at winter 2 and are switched to the alternative treatment. Data from the cross-over subjects will also be analyzed using mixed linear regression to compare within-person differences in pre-treatment biomarkers and their changes during their initial and subsequent treatments. Treatment, time point (winter 1 or 2), and their interaction will be included to test the effect of treatment sequence on within-person differences in biomarker responses to CBT-SAD and LT.

##### Aim 3

Logistic and linear regressions similar to those for Aim 1 will be used to compare the effect of switching from CBT-SAD➔LT versus LT➔CBT-SAD on winter 3 recurrence and depression scores. Post hoc adjustment for any differences between switch groups in baseline characteristics, treatment response, and biomarker profiles will be done by including them as covariates. Mixed linear regression will be used to longitudinally model depression scores over the three winters, with treatment as a time-varying covariate.

##### Aim 4

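### In Aim 2 the light-therapy (LT) arm's winter 2 biomarkers mix current light users with non-users, so the persistence and cross-over analyses cannot separate ongoing light from lasting change

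*Protocol article*

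**What the plan says.** The follow-up strategy in the LT arm is continued light. The section on post-trial care says that "LT subjects are encouraged to continue light therapy each fall/winter". The September letter to LT participants "encourages them to re-initiate daily LT upon onset of the first depressive symptom in the coming fall/winter", and the Light therapy section adds that "we will offer access to our light boxes to LT participants in winters 2 and 3". The background section reports that "only 41% of those treated acutely with LT continue using it over subsequent winters".

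Biomarkers are measured again in January of winters 2 and 3 (Winter 2 and 3 follow-up procedures). Under Biomarker assessments, the winter 2 follow-up is the only measurement between winter 1 treatment and a switch. The stated light controls are acute: 45 minutes of dim light plus 11 minutes of darkness before PIPR testing, and dim light during saliva collection.

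Aim 2 (Data analysis) uses the follow-up value in two ways. First, persistence of biomarker change is examined as a predictor of outcome. Second, in switched participants, pre-treatment biomarkers and changes are compared between the first and second treatment in a mixed model: "Treatment, time point (winter 1 or 2), and their interaction will be included to test the effect of treatment sequence on within-person differences". Adherence enters Aim 2 only in ancillary analyses. Adjustment for ongoing treatment at follow-up is described for some Aim 1 analyses, where the light example is "light therapy use in the CBT-SAD group".

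**The concern.** PAD and PIPR are the candidate biomarkers of light itself. A January value in someone using light daily shows the effect of current treatment. The same value in someone who has stopped shows whatever has lasted. Averaged over the LT arm and called persistence, the result depends on the share who happen to be using light.

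For LT-to-CBT-SAD switchers this mixed value is also the starting point of the second treatment. It can differ from the winter 1 pre-treatment value for reasons unrelated to lasting change. If light use then changes at the switch, the biomarker change during CBT-SAD would contain that change in light use. The stated model terms do not allow for either.

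At stake is the interpretation of the follow-up and cross-over parts of Aim 2: how stable LT's target engagement is, and whether biomarker response is treatment-specific within person.

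**Working it through.** **Reproducing the plan's figures (Sample size).** Projected recurrers: 80 × 45.6% = 36.5, about 37 (LT); 80 × 27.3% = 21.8, about 22 (CBT-SAD). Both match. Power for a 0.45 SD biomarker difference with 80 per arm, two-sided 5% assumed, is 81.2%, against the stated 80%.

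**Who is on light in January.** Let f be the share of LT participants using light at the winter 2 visit. Taking f = 0.41 from the background section:
- LT arm: 0.41 × 80 = 32.8, about 33.
- Projected LT recurrers: 0.41 × 37 = 15.2, about 15.

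**Apparent persistence.** Let d be the on-light change and p the fraction that truly lasts off light. Assume current users show the full d. The mean change at follow-up is d × [f + (1 − f)p]. With p = 0 the arm appears to retain f = 41% of d. For f from 20% to 80% it would appear to retain 20% to 80%, with nothing lasting.

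**Cross-over model.** Let L and C be the true changes under LT and CBT-SAD. Suppose, as an assumption, that light stops at the switch.
- LT first: L in winter 1; C − f·d in winter 2.
- CBT-SAD first: C in winter 1; L in winter 2.
- Treatment contrast averaged over winters: ½[(L − C) + (L − C + f·d)] = (L − C) + f·d/2.
- Treatment-by-winter contrast: (L − C) − (L − C + f·d) = −f·d. With two sequences this is the sequence term, so it cannot separate carry-over from ongoing light.

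If light use is the same before and throughout the second treatment, the −f·d disappears from the change. Only the winter 2 level is affected.

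**Illustration in SD units.** The article gives no on-light shift for PAD or PIPR. I assume d = 0.45 SD, L − C = 0.45 SD, p = 0, and correlations of 0.5 for levels and 0.3 for changes:
- f·d = 0.41 × 0.45 = 0.18 SD.
- Winter 2 against winter 1 pre-treatment level in 37 LT-first switchers: simulated rejection 18.5% instead of 5%.
- LT against CBT-SAD at follow-up, 80 per arm: rejection about 21%.
- If light stops at the switch: treatment contrast 0.45 + 0.18/2 = 0.54; the interaction rejects only 6.9% of the time, so it would rarely reveal the problem.

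Over f = 20–80% and d = 0.3–0.8 SD, f·d runs from 0.06 to 0.64 SD, rejection in the pre-treatment comparison from 6% to 95%, and rejection of the interaction from about 5% to 30%. With f = 0, error rates return to about 5% and the contrast is unbiased.

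**The case against.** The best defence is that continued light is the intended LT strategy, so stability while using light is a legitimate quantity and the article never claims off-light persistence. That stands, and it is why the fix relabels the overall figure and does not replace it. It does not help the cross-over analysis, where the same value serves as a pre-treatment baseline.

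It is also fair that Aim 2 leads with the winter 1 model of change during treatment, that the article itself presents the interaction as a test of sequence, and that further covariates could be set in an analysis plan not shown. But the article does fix the terms of the cross-over model. Its ancillary adherence analysis is not defined as light use at the winter 2 visit: the adherence section describes attendance, homework, and light-box logger and diary data.

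A reader might infer more than the document supports:
- That a one-hour bias follows. The one-hour shift in the Light therapy section is in the temperature minimum. PAD is melatonin onset relative to mid-sleep, and PIPR is not measured in hours, so the figure does not carry over.
- That a light effect will be credited to CBT-SAD. This requires light use to change at the switch, which the article does not state.
- That Aim 2 winter 3 biomarker results are affected. No Aim 2 model is said to use winter 3 biomarkers.
- That light use should be a covariate in every model. The letter ties restarting to the first symptom, so adjusting for it in models of depression or recurrence conditions on a symptom-driven, post-randomisation variable and may remove part of LT's own effect.
- That a missing washout is an error. Follow-up is meant to reflect continued treatment; no washout is proposed here.

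**Conclusion.** The point holds for the winter 2 biomarker analyses of Aim 2. As stated, the persistence and cross-over analyses cannot tell current light from lasting change in the LT arm. At 41% use, about 33 of 80 LT participants and 15 of 37 projected LT recurrers are affected, and about 41% of the on-light change would appear retained even if none lasted.

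This rests on a background continuation figure. Use in this trial, with prompts and boxes offered, may differ, and use among recurrers is unknown. It also assumes that current users show the full on-light effect. The size in PAD or PIPR units cannot be derived from the article, and the SD figures above are illustrations. A spurious change during CBT-SAD is conditional on what happens to light use at the switch. Aims 1 and 3, as comparisons of treatment strategies, are not undermined.

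**What to change.** 1. Report LT-arm biomarker change at winter 2 separately for current light users and non-users: yes/no from the treatment-utilisation questionnaires, with minutes if available. Describe the overall figure as stability under the continued treatment strategy.
2. Add current light use as a covariate in a sensitivity version of the cross-over model, where the biomarker is the outcome. Do not make it a mandatory covariate in models predicting depression or recurrence.
3. Rest claims of treatment-specific PAD and PIPR engagement on the randomised winter 1 comparison, where prior LT is an exclusion, with cross-over data as supportive.
4. State what the protocol expects of light use when an LT participant switches to CBT-SAD, and reconcile this with the post-trial care text. No clinical rule is proposed here.

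The cost is analysis wording and two extra summaries. The questionnaires are already given at follow-up, though the article does not say that they record minutes per day, and no logger is described for boxes that participants buy. Light use is self-selected and symptom-driven, so the split is observational and should be labelled so.

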### Trial design {8}

This is a head-to-head confirmatory efficacy trial comparing CBT-SAD and LT (with equal-probability allocation) designed to test superiority of one treatment over the other in depression recurrences at winter 2 follow-up. Participants with recurrences at winter 2 follow-up will be offered the opportunity to cross-over into the alternate treatment. All participants are followed-up at winter 3 (Fig. 1).

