### Sample size {14}

With a target *N* = 160 (80 subjects in each of the two treatments), the study will have 80% power to detect main effect differences of 22% (e.g., 28% vs. 50%) in winter 2 recurrence, which we expect at a naturalistic follow-up [14, 44]. Sample sizes for comparisons of winter 3 recurrence will depend on the number of recurrences at winter 2. Based on the recurrence rates observed in our prior study, we project that there will be about 37 recurrences in the LT group and 22 recurrences in the CBT-SAD group. This will provide 80% power to detect a difference in winter 3 recurrence of 35% (e.g., 60% vs. 25%) between CBT-SAD➔LT and LT➔CBT-SAD and a difference of 27% (e.g., 23% vs. 50%) between CBT-SAD and LT subjects without winter 2 recurrence. For biomarker comparisons, there will be 80% power to detect differences of 0.45 standard deviation (SD) in post-treatment values or in pre-post treatment changes between CBT-SAD and LT. Power for detecting relationships between biomarkers and outcomes were based on the odds ratio associated with an increase of 1 SD in the biomarker value or its change. For post-treatment remission, there will be 80% power to detect an OR of 2.2 in the CBT-SAD or LT group and a 2.4-fold difference in the ORs for the two treatments. For winter 2 recurrence, there will be 80% power to detect an OR of 2.2 in the LT group, an OR of 2.8 in the CBT-SAD group, and a 2.9-fold difference in their ORs. There was minimal attrition (4.5%) in our previous study, and we anticipate similar retention in this study. However, with attrition as high as 20%, there will be 80% power to detect a difference in winter 2 recurrence of 24% between CBT-SAD and LT and a difference of 39% in winter 3 recurrence between the two switch groups. Empirical sample size estimates^21^ indicate that the study will have at least 80% power to detect a mediated effect if the regression coefficient for the direct effect of treatment after adjustment for the mediator is at least .39 and the coefficients for the effect of treatment on the mediator and the effect of the mediator on outcome after adjustment for treatment are at least .26.

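### Aim 3 lets observed differences between two non-randomised switch groups choose the covariates, so severity at the switch is not guaranteed in the winter 3 models and measurements taken after the switch are not ruled out

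*Protocol article*

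**What the plan says.** All references are to the protocol article.

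- **How the groups arise.** Trial design {8}: "Participants with recurrences at winter 2 follow-up will be offered the opportunity to cross-over into the alternate treatment". Membership of a switch group depends on recurring after the first treatment and on accepting an offer. There is no second randomisation.
- **How large they are.** Sample size {14}: "we project that there will be about 37 recurrences in the LT group and 22 recurrences in the CBT-SAD group". The same section claims 80% power for winter 3 recurrence of 60% vs 25%.
- **The main Aim 3 models.** Statistical methods {20a}: "Logistic and linear regressions similar to those for Aim 1 will be used to compare the effect of switching from" one treatment to the other, on winter 3 recurrence and depression scores. The only covariates named for Aim 1 concern concurrent treatment: "Covariates will be included in some analyses to assess the effect of treatment on outcomes after adjustment for any ongoing treatment reported at follow-up". No severity score is named.
- **The adjustment rule.** Aim 3: "Post hoc adjustment for any differences between switch groups in baseline characteristics, treatment response, and biomarker profiles will be done by including them as covariates".
- **A further Aim 3 model.** "Mixed linear regression will be used to longitudinally model depression scores over the three winters, with treatment as a time-varying covariate".
- **What is measured at the switch.** Winter 2 and 3 follow-up procedures: "Follow-up assessments will occur in January of the next two winters (in winters 2 and 3"), and "Participants will be interviewed by a clinical graduate student blind rater with the SIGH-SAD". Table 1 repeats the mid- and post-treatment assessments in winter 2 for those who switch, so response and most biomarkers are recorded for both treatment courses.

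**The concern.** Randomisation does not balance the switch groups. People who recur after CBT-SAD may differ in prognosis from people who recur after LT, so severity at the switch is a possible confounder as well as a source of precision. Under the stated rule it enters only if the groups are seen to differ. With 59 people, failure to see a difference says little about whether there is one, and the covariate set is settled by the data being analysed.

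The list of what may enter is also loose about time. Response to the winter 1 course precedes the switch and is a legitimate covariate. Response to the winter 2 course, and biomarkers recorded during or after it, follow the switch and lie on the path to the winter 3 outcome. Conditioning on them would change what the comparison estimates. The text does not separate the two.

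**Working it through.** **Inputs.** Group sizes 22 and 37, rates 60% and 25%, and target N = 160 come from Sample size {14}. The prior recurrence rates of 27.3% and 45.6% come from Background {6a}. The recurrence threshold (SIGH-SAD ≥ 20, with HAM-D and atypical minima) comes from Outcomes {12}. Assumptions not in the document: two-sided alpha 0.05; a difference means p<0.05 on a t-test; correlations of 0.3 to 0.7 between the score at the switch and the winter 3 outcome.

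**1. The plan's own figures.** 80 × 0.273 = 21.8 and 80 × 0.456 = 36.5, matching about 22 and 37. For 60% vs 25%:

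- Unpooled SE = √(0.60×0.40/22 + 0.25×0.75/37) = 0.126. Power = Φ(0.35/0.126 − 1.96) = 79.1%.
- The pooled-variance version gives 77.1%.

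The stated 80% is reproduced approximately. It is an unadjusted calculation, so it does not bear on the covariate rule.

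**2. How often an imbalance is noticed.** Noncentrality = δ/√(1/22 + 1/37) = δ/0.269, with 57 degrees of freedom.

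- δ = 0.5 SD: noncentrality 1.86, flagged 45% of the time.
- δ = 0.3 SD: noncentrality 1.11, flagged 19% of the time.

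**3. What adjusting only if different leaves behind.** Simulation of a linear outcome, 40,000 runs per row, no true switch effect:

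| Correlation | True imbalance | Bias, never adjusted | Bias, adjusted if p<0.05 | Bias, always adjusted | Type I error, adjusted if p<0.05 |
|---|---|---|---|---|---|
| 0.3 | 0.3 SD | 0.09 | 0.05 | 0.00 | 5.1% |
| 0.3 | 0.5 SD | 0.15 | 0.05 | 0.00 | 5.3% |
| 0.5 | 0.3 SD | 0.15 | 0.08 | 0.00 | 5.2% |
| 0.5 | 0.5 SD | 0.25 | 0.09 | 0.00 | 6.0% |
| 0.7 | 0.3 SD | 0.21 | 0.12 | 0.00 | 5.4% |
| 0.7 | 0.5 SD | 0.35 | 0.12 | 0.00 | 6.4% |

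**4. Power for recurrence, the endpoint on which Aim 3 is powered.** Simulated logistic regression with a likelihood-ratio test, 22 vs 37, 60% vs 25%, with winter 2 severity correlated with a latent winter 3 severity:

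- Correlation 0.3: about 78% unadjusted, about 80% always adjusted.
- Correlation 0.5: about 78–80% unadjusted, about 84–86% always adjusted, a gain of about 6 points. The ranges reflect simulation runs; with the marginal rates fixed, true unadjusted power does not depend on the correlation.

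**5. Which correlation is plausible.** Everyone who switches has passed the recurrence threshold, so the score's range is cut. As a rough guide, treat the projected 59 of 160 (37%) as the top of a normal distribution. The variance ratio is then v = 0.297, and a full-sample correlation r becomes r√v/√(1 − r² + r²v). For r = 0.5 this is 0.272/0.908 = 0.30.

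**6. Events available.** 22 × 0.60 + 37 × 0.25 = 13.2 + 9.25 = 22.45, so about 22 winter 3 recurrences to support the logistic model.

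**The case against.** The strongest reply is that Aim 3 does not ignore winter 2 severity. The mixed model over three winters carries winter 2 scores as repeated outcomes and draws on the within-person correlation. This stands for the score outcome. It does not reach the winter 3 recurrence comparison or the single-time-point linear regression.

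The protocol names no significance test for a difference, so the 45% and 19% belong to an assumed rule. That also stands. Even under that rule, the residual bias and the inflation of type I error are small.

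Winter 2 severity might be counted among baseline characteristics, and covariate lists are commonly left to an analysis plan, which is not shown here. But this text goes further than leaving the list open: it makes entry depend on observed differences, and an analysis plan would have to reverse that.

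Some stronger readings are tempting and are not supported:

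- **The plan adjusts for a mediator and biases the effect toward zero.** Winter 1 response is a natural reading of the sentence, and it precedes the switch. The text permits the other reading but does not state it. The direction of any bias is not established either.
- **About 10 points of power are lost, 80% against 90%.** That figure applies to a score comparison at 0.77 SD with an assumed correlation of 0.5. The stated power is for recurrence, and the mixed model already serves the scores.
- **The score at the switch is the strongest predictor available.** Nothing in the document shows this, and the restricted range argues for caution.
- **The whole model is chosen after seeing the data.** The base comparison is fixed by reference to Aim 1; the covariate set is what remains open.

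**Conclusion.** The concern holds in a limited form. For two non-randomised groups of about 22 and 37, the protocol fixes a data-driven covariate rule. It does not guarantee the winter 2 SIGH-SAD in the recurrence model or the single-time-point score regression, and it leaves treatment response and biomarkers undated relative to the switch.

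The size is modest: residual bias of about 0.05 to 0.12 SD under a p<0.05 screen and correlations of 0.3 to 0.7, and a power gain for recurrence of about 2 to 6 points from always adjusting. The protocol gives no correlation, and the recurrence threshold favours the lower end. Aim 3 is not the primary analysis, and adjustment reduces but does not remove confounding by selection into the switch. The change is still worth making, because Aim 3 is a named aim with a directional expectation and the remedy is cheap.

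**What to change.** Replace the adjustment sentence in Aim 3 with a prespecified rule:

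1. The logistic model for winter 3 recurrence and the linear model for winter 3 scores always include the winter 2 SIGH-SAD at the switch, as the one prespecified covariate beside switch group.
2. Covariates are not selected on observed differences between the switch groups.
3. Treatment response and biomarker values used as covariates are limited to those measured before the second treatment starts.
4. All further covariates go to a labelled sensitivity analysis, because about 22 expected events will not support an open list.
5. The report states that the switch groups are not randomised and that adjustment does not remove selection.

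The cost is analysis-plan wording only. The measures are already on the assessment schedule, so no added visit or instrument is needed. The wording should be settled before winter 3 outcomes are examined.
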